### Dietary intervention

The dietary intervention consist of an ad-libitum self-served school lunch in the intervention schools during a 6-month period. The school lunch will be developed to be nutritionally balanced and tasty.

About 80% of all available options per week will be healthy choices according to the Dutch Nutritional Guidelines based on their levels of saturated and trans fat, added sugar, salt, dietary fibre, and energy density [20]. The daily basis of the lunch is whole-grain bread slices with sandwich fillings. Every day, raw (snack) vegetables will be provided (50 g per child per day). In addition, there will be a special lunch item, such as a vegetable soup, fruit or a boiled egg every day. In two of the three schools, there will be no lunch at Wednesday as children go home early in the afternoon.

Two lunch menus are developed for three weeks that will be repeated in a three month cycle. A dietician and nutritionist will be involved to create the menu. The menus will be inspired by a qualitative study among children, parents and school staff [21], experts and chefs who provided input during workshops to make sure that the lunch options are healthy, varied and tasty. Religious or allergy-related restrictions will be taken into account. Teachers or support staff will be trained to order foods each week in a specially developed ordering system. In consultation with the school it will be determined how the lunch is organized logistically and practically. This is possible, for example, with volunteers such as parents or support staff who are already working at school. Members of the research team will visit schools regularly to provide support on this process. In case a product will be disliked by a large number of children even after repeated exposure, it will be replaced by another product. This will be decided based on these school visits by members of the research team.

Children consume the lunch in the classroom, which is similar to where they eat their current packed lunch from home. During the intervention, all children receive a cup and a lunch box that can be used as a plate to eat from during lunch. Children bring this lunch box and cup home to be cleaned and bring it back to school the next day. Equipment such as a fridge and serving plates to be put in school or classroom will be bought by the project team if needed. Children will be able to select lunch with food of high nutritional value by walking along a buffet at which all options are displayed. The buffets are displayed in the class room (one school) or in a central place in the school (two schools). Teachers are free to organize distribution in different ways, for example by putting products at groups of desks. Ideas and inspiration for healthy toppings on bread will be provided to the children by means of printed placemats and posters that will be displayed during lunch. Children are still allowed to bring a lunch item from home if they would like. Responsible school staff will receive instructions on how to deal with food safety by visits of the research team.

### Outcome measures

#### Consumption and evaluation of lunch by children

At baseline, lunch intake data of vegetables, bread, toppings, drinks and additional products (e.g. snacks) will be collected as primary outcome measures within one month before start of the school lunch. To assess lunch intake at school, the lunch of each child will be photographed just before and after consumption, and lunch components will be noted on an observation form. At baseline, children will be asked to open their lunch box and drink cup so that the products can be photographed. For different classes and schools this will be done at different weekdays to capture the variation in food offerings. Each product in the lunch box and drink cup will be classified on its healthiness by using the criteria of the Dutch nutrition guidelines: fit within recommended Wheel of Five, weekly choice or daily choice. We consider the food groups ‘vegetables’, ‘whole grain bread’ and ‘milk products and tea without sugar’ as healthy, given that they are included in the Wheel of Five, the Dutch national counselling model based on their association with a reduced risk for chronic diseases. Food groups which are advised to be limited are considered unhealthy, such as processed meats and sugar sweetened beverages [22]. For all the products, an estimation of consumption amounts will be made based on the pictures and an observation form [23]. No software will be used to determine portion size. Observers record the type of drink present and also provide an estimation of the portion size (i.e. about 200, 300, 500 ml), number of bread slices with topping present, margarine or butter spread. This measure will be repeated at T1 (after three months) and T2 (after six months, see also Table 1).

**Table 1 Tab1:** Overview of included outcome measures (children)

Outcome measures	Time of measurement	T1 (after 3 months)	T2 (after 6 months)
	Baseline T0		
*Primary outcome measures child*			
- Lunch intake: observation by photographing lunch with questionnaire among children	X	X	X
*Secondary outcome measures child*			
- Evaluation and satiation after lunch: questionnaire among children	X	X	X

The secondary outcome measures for children will be collected by means of a questionnaire and involve their evaluation of the lunch and the post-lunch satiation they experience. The evaluation of the school lunch was added by the item ‘The lunch was tasty’ and ‘We had a good time during lunch’ (5-point scale). An item was included to assess the time to eat the lunch: ‘I had enough time to eat’. Response categories will be depicted via smiley faces. After introduction of the school lunch, the following items will be added to evaluate the school lunch ‘there is enough choice at lunch’, ‘I like it to prepare my own sandwich in class’, and ‘I prefer to bring my own sandwiches from home’.

To assess children’s evaluation of the quantity of lunch consumed, children will be asked the question ‘How much did you eat’ with three answer categories: ‘too little’, ‘sufficient’ and ‘too much’. To measure overall satiation after lunch, we use the specifically designed measurement instrument of Faith and colleagues [24] who use an ordinal silhouette scale with increasing numbers of circles in the stomach region to indicate increasing levels of fullness.

In the follow-up questionnaire, children will provide their age, gender and ethnicity. Children will complete the survey on their own in the classroom after lunch. Questionnaires will be administrated using EyeQuestion software at Lenovo tablets. A similar data collection procedure will take place after three months (T1) and six months (T2). At those time points, questions will be added about whether they have eaten the products of the lunch menu and their evaluation of these products.

#### Evaluation of school lunch and compensation effects as assessed by parents

A questionnaire will be administrated among parents of the three intervention schools and three comparison schools to assess potential compensation effects. Potential compensation effects due to the school lunch are probably small. To be able to measure these small effects on total dietary intake per day, several full measuring days would be required per child which makes it unlikely that the majority of children and parents would participate in extensive dietary intake measures (especially for control schools). If there are any compensation effects after school, then parents are probably the first to notice. That is why we have opted for a direct method of explicitly asking parents if they see differences in their child’s dietary intake. As parents of intervention schools are aware of the objective of the healthy school lunch, they could be more inclined to give socially desirable answers. Therefore, it is important to compare their answers with parents from schools without intervention.

To better understand how parents evaluate the school lunch and perceive their children’s eating and drinking during school lunch, one group discussion with parents at each of the intervention schools will be conducted.

##### Brief questionnaire on potential compensation effects

This questionnaire focuses on parents’ perception of changes in consumption outside school hours during the final month of the school lunch period. To increase the response rate, the questionnaire was kept very brief and were told to keep their oldest child at primary school in mind. Questionnaires will be distributed both via school e-mail and paper.

First, parents will be told the following: ‘We are curious to know whether your child started to eat differently during the past six months (since autumn holiday till now). Could you indicate whether your child eats less, about the same or more of the following products at home compared to six months ago? If you do not know, then you fill in ‘I do not know’. The following products were then mentioned: ‘snack vegetables, such as tomatoes, cucumber, radish, carrot’, ‘vegetables during the evening meal, warm or cold such as lettuce and salad’, ‘sweet snacks such as cookies, chocolate or candy’, ‘savory snacks, such as crisps, cheese or warm snacks’, ‘juice, lemonade or soft drinks with sugar (no diet)’ and ‘water, milk and sour milk’. Answer possibilities will be: ‘eating less’, ‘eating about the same’, ‘eating more’ and ‘I do not know’.

Next, parents will be asked ‘Does your child has now more or less appetite (desire for food) immediately after school compared to six months ago?‘ with answer options ‘now less appetite’, ‘about the same appetite’, ‘now more appetite’, and ‘I do not know’. The same question was asked regarding appetite during the evening meal.

Finally, parents were asked to indicate the group of their oldest child at the school and were given the opportunity to comment to the question: ‘Are there other things that you noticed with regard to the eating behavior of your child in the past six months? For example, are there foods or drinks your child asked for or talked about? Do you have any more suggestions or questions for the researchers?’

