## Methods

### Study design

In the Healthy School Lunch project children in grades 5–8 (aged 8–12 years) of three primary schools in the Netherlands will receive a healthy school lunch for a 6-month period (November 2018 to April 2019). The development of this healthy school lunch is guided by a study among parents and children about desired school lunch concepts [16, 17]. Important to note is that in the Netherlands, it is very common for children to take all their foods and drinks from home (morning snack and lunch). There is no opportunity to buy food or drinks at primary school and there is no national subsidized school lunch program which offers school meals. Most primary schools in the Netherlands report to have a written food policy (e.g. on what is allowed to bring) although there is no legal obligation to do so [18].

To answer research question 1, we will collect lunch consumption data by means of pictures. All intervention group children will have to complete an initial baseline measurement in the situation where they still bring their own packed lunch. They will also have to complete a second and third follow-up questionnaire at month 3 half-way and month 6 at the end of the period in which a healthy school lunch will be provided.

To answer the second research question, a quasi-experimental, intervention-comparison group design (3 intervention schools and 3 comparison schools) will be carried out. There will be no randomization of the intervention and comparison schools, as the schools had to fully agree and decide on their participation beforehand, which required consent from their stakeholders (teachers, parents, support staff). Potential compensation effects will be measured with a single brief questionnaire among parents both at the three intervention schools and at the three comparison schools at month 6 of the lunch period. The school lunch will also be evaluated by parents (discussion groups) and teachers and support staff (brief questionnaire).

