Schools were situated in the capital of the Netherlands Amsterdam and in two small cities, i.e. Lunteren and Vlaardingen (10.000–100.000 inhabitants). Two of the three schools are situated in a district characterized by residents with a lower SEP (Amsterdam and Vlaardingen) and one in a semi-rural town with children of parents with a relatively high SEP (Lunteren). Comparison schools were recruited to match these SEP levels. All children of grades 5 till 8 were invited to participate in the study. Children of grades 1 to 4 were not invited. This was done given budget constraints and we expected that older children would be better able to reflect on their experiences in the questionnaire. Children and parents who decided to join the lunch after the start will also be enrolled. Consequently, data at baseline can be missing for these children. Letters will be sent to parents to explain the study and school lunch. At each school, information meetings will be set up to inform all parents and children. All parents of children that participate will be send a letter after about three months with an invitation to give feedback about the school lunch. This evaluation is not part of the measures, but will be used to adapt and improve the intervention if necessary.

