#### Evaluation of school lunch and compensation effects as assessed by parents

Descriptive statistics will be used to examine the compensation questionnaire among parents. Chi-square tests of independence will be computed for ordinal answers on compensation questions in the questionnaire to identify statistically significantly differences among parent groups (comparison versus intervention schools).

Each session of the group discussions with parents will be audiotaped. During the sessions, notes will be taken by at least two researchers. After the discussion, these two researchers will discuss and summarize their main findings.

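### The compensation comparison is not restricted by grade, so any intervention-school questionnaires about grade 1–4 children would count as exposed and pull the result towards no compensation

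*Protocol article*

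**What the plan says.** Exposure is set by grade. Under Study design, "children in grades 5–8 (aged 8–12 years) of three primary schools in the Netherlands will receive a healthy school lunch for a 6-month period". Under Recruitment, "Children of grades 1 to 4 were not invited".

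The recipients of the parent questionnaire are set by school: "A questionnaire will be administrated among parents of the three intervention schools and three comparison schools to assess potential compensation effects". The distribution route carries no grade limit either: "Questionnaires will be distributed both via school e-mail and paper".

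The child whom the parent describes is set by birth order. Respondents "were told to keep their oldest child at primary school in mind". The form also records the child's grade, since "parents were asked to indicate the group of their oldest child at the school".

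The contrast is set by school. The Data analysis section plans chi-square tests to find "statistically significantly differences among parent groups (comparison versus intervention schools"). It gives no rule for using the reported group. The questionnaire, as described, has no item on whether the child took part in the lunch.

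**The concern.** Three definitions do not line up: exposure follows grade, the described child follows birth order, and the comparison follows school. A family at an intervention school whose oldest pupil is in grades 1–4 would answer about a child who was never offered the lunch. Taken literally, the analysis section counts that answer as intervention.

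Such answers carry no effect of the lunch, so they pull the difference between school types towards zero. Compensation is one of the study's two research questions, the article itself expects any such effect to be small, and a null result would be read as good news about the lunch. The error would therefore favour the reassuring conclusion.

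**Working it through.** **The plan's own figure.** The only sample size in the article, 134 children, belongs to vegetable consumption at lunch (6.7% against 13.4%, power 0.8, two-sided 0.05). It reproduces as a one-sample test against a fixed rate: [(1.960·√(0.067·0.933) + 0.842·√(0.134·0.866)) / 0.067]² = 134.4. It says nothing about the parent questionnaire, for which the article states no sample size, so what follows is illustrative.

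**Inputs, all assumed.** f is the share of questionnaires that describe a grade 1–4 child, taken as equal in both arms and set at 20%, 30% and 40%. There are 150 questionnaires per arm. The proportion answering that the child eats more of some product is 10% without exposure and 22% with it. The test is two-sided at 0.05, with clustering by school ignored.

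On the range for f: if all families were surveyed and answered equally, a simple count over eight equal grades puts the oldest pupil in grades 1–4 in 4 of 8 positions for one-child families. It is 4 of 10 or 4 of 11 for two children spaced two or three grades apart, and 4 of 12 for three children spaced two apart. That is about 0.33 to 0.50. If only grade 5–8 families were surveyed, f is 0.

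**Formulas.**
- Diluted difference = (1 − f) × true difference.
- Diluted intervention proportion = 10% + (1 − f) × 12 points.
- Restricted number per arm = (1 − f) × 150.
- Power = Φ[(d − 1.96·SE₀)/SE₁], where SE₀ uses the pooled proportion and SE₁ the separate ones.

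**Results.** With f = 0, power is 81%.

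| f | Diluted contrast, 150 per arm | Power | Restricted contrast, 10% vs 22% | Power |
|---|---|---|---|---|
| 20% | 10% vs 19.6% | 65% | 120 per arm | 72% |
| 30% | 10% vs 18.4% | 55% | 105 per arm | 66% |
| 40% | 10% vs 17.2% | 44% | 90 per arm | 59% |

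**Efficiency.** Information about the effect is roughly proportional to n(1 − f)² when unexposed children are included and to n(1 − f) after restriction. The gain from restricting is the ratio, 1/(1 − f): 1.25, 1.43 and 1.67 times.

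**A smaller effect.** With 10% versus 15%, 150 per arm and f = 40%, power is 13% diluted and 17% restricted, against 26% with no dilution. Restriction adds little power here, but the estimate is no longer shrunk from 5 points to 3 (0.6 × 5).

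**The case against.** The strongest objection is that only grade 5–8 families may have been surveyed. The limitations paragraph of the Discussion describes the intervention and comparison schools as taking part with grades 5 to 8, and the parent questionnaire is the only data collection described for the comparison schools. Recruitment likewise invites grades 5 to 8 only. A population set for the whole study need not be repeated in each subsection, and the oldest-child rule also makes sense for families with two children in the upper grades. This stands as far as it goes: a reader might infer that grade 1–4 parents were surveyed and that dilution has occurred, but the article does not say so. It does not settle the matter the other way. The questionnaire and analysis sections do not apply the limit, Recruitment refers specifically to parents of participating children when it means only them, and the form asks for the child's group.

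A second objection is that an analysis filter is a detail for an analysis plan that is not shown. An unstated filter alone would not be a finding. Here, however, the article does fix the recipients, the described child and the contrast, and taken together they do not match the exposure.

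A third objection concerns size. It is tempting to quote 1/(1 − f)², that is 1.56 to 2.78 times as many parents. That is the cost of dilution against a fully exposed sample of the same size. Restriction also discards answers, so it recovers only 1/(1 − f).

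Finally, the oldest-child rule moves answers towards the exposed grades, and the Discussion calls compensation a secondary objective. Both are right. The first lowers f without making it zero, and the second means that the primary lunch-intake outcome is unaffected.

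**Conclusion.** The point holds in conditional form. As written, the compensation contrast admits children who could not have received the lunch and counts them as intervention. If parents whose oldest pupil is in grades 1–4 answered, the difference between school types shrinks by the share f, towards no compensation. The documents do not support the flat statement that this has happened.

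For an assumed f of 20–40%, the loss is 7 to 15 percentage points of power relative to the restricted analysis (65% against 72%, up to 44% against 59%), or 1.25 to 1.67 times in efficiency. These figures rest on an assumed f, 150 per arm, 10% versus 22%, and no allowance for clustering within six schools. With the small effects that the article expects, the power argument weakens, and the main reason for the change is removal of the grade-based bias.

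**What to change.** State in the Data analysis section on parents that the main compensation comparison uses, in both arms, only questionnaires whose reported group is 5–8, with all questionnaires as a sensitivity analysis. Also state which families were sent the form; if only grade 5–8 parents were, one sentence saying so closes the point.

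Report lunch participation in grades 5–8 for each intervention school. The filter cannot remove dilution from grade 5–8 children who did not join, and the participation rates let a reader judge how much remains.

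The cost is a somewhat smaller analysed number. Data collection is already complete and analysis is under way, but the filter uses an item already on the questionnaire, so it needs no new data.

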##### Group discussion on evaluation school lunch

At each intervention school, a group discussions will be conducted using an interview guide (Table 2). This semi-structured interview guide contains both closed- and open-ended questions. The discussions will take place at school after school hours in the afternoon and evening and will be facilitated by at least two researchers. Discussions will take about 45 min and will be audiotaped. Parents will be recruited at school on a convenience basis using the school newsletter and posters.

**Table 2 Tab2:** Interview guide for parents’ group discussion

Stage	Content
1) Introduction and welcome	Informed written consent, explanation of discussion topic and rules, introduction of participants
2) Parents’ general school lunch evaluation	Individual task: Rating of three statements Group discussion of task
3) Perceptions of child’s eating and drinking during school lunch	Individual task: Rating of four statements Group discussion of task
4) Questionnaire	Individual completion of questionnaire with demographics.

First, participants will be to provide written informed consent. After a warming up round of introductions of each participant, they will asked about their general evaluation of the provided school lunch by responding individually to four statements: ‘My child is satisfied with the school lunch’, ‘I am satisfied with the school lunch’, ‘My child prefers a home-brought lunch’ and ‘I prefer a home-brought lunch’. Each statement has to be evaluated on a 3-point scale (disagree, do not know/in doubt, agree). Subsequently, the moderator will ask participants to discuss their responses to the statements plenary. Follow-up questions will be used to gain more in-depth insights.

Next, participants will be asked to indicate individually the level of disagreement or agreement to the statement ‘My child eats and drinks …. during lunch at school’, followed by ‘healthy’, ‘sufficiently’, ‘tasty’ and ‘varied’ on a 3-point scale (disagree, do not know/in doubt, agree). Answers will be discussed in the group. Participants were probed for the underlying reasons for their answer. Finally, each participant will complete a background questionnaire to determine age, gender, group and age of children and highest completed educational level of the participating parent. Participants will receive a small gift.

